## Abstract

**Background:**

The incidence of occupational hand eczema is approximately 0.32 per 1,000 person years. The burden of the disease is high, as almost 60% has eczema-related sick leave during the first year after notification, and 15% are excluded from the workforce 12 years after disease onset. New treatments and prevention strategies are needed.

**Methods/Design:**

*Trial design:* The PREVEX trial is a randomised, parallel-group, superiority trial.

*Participants:* All individuals from the Capital Region of Denmark and Region Zealand with a suspected occupational skin disorder notified to the National Board of Industrial Injuries between June 2012 and December 2013 are invited to participate in the trial. Inclusion criteria are: self-reported hand eczema and informed consent. Exclusion criteria are: age <18 years or >65 years; permanent exclusion from the workforce; inability to understand the Danish language; any serious medical condition; and lack of written informed consent. We plan to randomise 742 participants. *Interventions:* The experimental intervention is an educational course in skin-protective behaviour and written information about skin care related to the participants' specific occupation. Also, a telephone hotline is available and a subgroup will be offered a work-place visit. The experimental and the control group have access to usual care and treatment. All participants are contacted every eighth week with questions regarding number of days with sick leave or other absence from work. 12 months after randomisation follow-up is completed. *Objective:* To assesses the effect of an educational course versus treatment as usual in participants with newly notified occupational hand eczema. *Randomisation:* Participants are centrally randomised according to a computer-generated allocation sequence with a varying block size concealed to investigators. *Blinding:* It is not possible to blind the participants and investigators, however, data obtained from registers, data entry, statistical analyses, and drawing of conclusions will be blinded. *Outcomes:* The three co-primary outcomes, assessed at 12 months, are: total number of self-reported days with sick leave; health-related quality of life; and subjective assessment of hand eczema severity. Explorative outcomes are: self-reported eczema-related sick leave, absence from work registered by the DREAM-register and by self-report, risk behaviour, knowledge of skin protection and performance management (self-efficacy; and self-evaluated ability to self-care).

**Discussion:**

The PREVEX trial will be the first individually randomised trial to investigate the benefits and harms of group-based education in patients with newly notified occupational hand eczema.

**Trial registration:**

ClinicalTrials.gov Identifier: NCT01899287

## Background

Occupational hand eczema is the most frequently recognised occupational disease in Denmark [1]. The incidence is approximately 0.32 per 1,000 persons in the total population [2], and the numbers are comparable in most of the industrialised world [3].

In 2011, the Danish National Board of Industrial Injuries recognised a total of 1,395 individuals with occupational skin diseases, and the large majority of these patients (> 90%) had occupational hand eczema.

Hand eczema affects mainly young people as 1/3 has onset of disease before the age of 20 years [2]. The lifetime prevalence is almost twice as high in women as it is in men [1]. This is mainly due to women’s higher exposure to wet work, occupationally as well as privately, which are well known risk factors [3]. Other aggravating factors are atopic dermatitis and contact allergy [1].

Hand eczema often takes a chronic course. A Swedish follow-up study reported active eczema 12 years after onset of disease in 72% of the sample of patients and found that 15% had been excluded from the work force [4]. In a Danish study, similar data were reported [5,6]. During a one-year period, 20% of patients with notified hand eczema had sick leave for more than five weeks due to skin disease, and 20% to 25% had loss of job (examined in the time span between notification and recognition). 57% had sick leave because of skin disease during the first year after notification. These data show that the burden of the disease is high in a personal as well as in a socio-economic context [7]. The number of persons with occupational hand eczema has remained unchanged despite public initiatives to reduce exposures to harmful allergens [8].

### Current treatment and prevention

In Denmark, there is no standard for secondary prevention of occupational hand eczema. However, operational guidelines for the diagnostic evaluation and treatment of hand eczema exist [9]. The guidelines recommend that advice should be given about personal protective equipment (e.g., gloves), and skin care with moisturisers.

In Germany, a course is offered to all health-care workers with occupational skin disease [10]. Persons with notified skin diseases are immediately after the notification invited to attend a two-day skin-protection course. The course is organised in cooperation with dermatologists, allergologists, occupational medicine specialists, hygiene specialists, and other staff members. The course includes a medical examination by a dermatologist, topics on medical history, atopic disposition, further diagnostics, therapy, skin protection, and an assessment of the patient’s ability to remain in her/his job. All findings by the physician are forwarded to the authorities, and they are the basis for the further treatment possibilities offered to the patient. This includes, in the most severe cases, initiation of a 3-weeks inpatient treatment programme. An observational study found that the course improved skin care and skin-protection behaviour, hand eczema, and quality of life one year after the course compared to before the course [11].

### Clinical data

A systematic review of randomised trials and controlled trials from 2010 assessed prevention programmes compared to no intervention or treatment as usual in participants with hand dermatitis [12]. The reviewers included seven trials. No meta-analyses were conducted, as the reviewers assessed the trials to be too heterogeneous with regard to populations, interventions, control groups, and outcome measures. Overall, the reviewers concluded that there was moderate evidence for the effect of preventive programmes on occurrence of hand dermatitis and adherence to preventive measures, and low evidence for improving clinical outcomes and self-reported outcomes. Furthermore, none of the included trials had ‘low risk of bias’ in all assessed domains, and the review was restricted to publications in English, with a high risk of publication bias. Also, the review did not distinguish between primary and secondary prevention trials.

We therefore conducted an updated search for randomised and controlled trials in hand eczema patients in December 2012 in the PubMed database. From this search, we identified two randomised trials with focus on secondary prevention by educational programmes in hand eczema patients. Both of these trials applied individual randomisation. One trial found that an individual intervention among health-care workers with self-reported hand eczema increases the participants’ use of preventive measures and improves hand eczema and quality of life compared with no intervention [13,14]. The other trial [15,16] found that patients with HE responded positively to integrated care carried out by a multidisciplinary team with respect to clinical severity, but the intervention did not significantly influence quality of life (QoL) or sick leave.

We identified nine other trials with focus on secondary prevention of hand eczema by educational programmes in various working groups. Overall, they have found a positive effect of *secondary* skin protection programmes on occupational hand eczema in patients from different professions such as health care workers [17-23], gut cleaners [24], and workers in the cheese-dairy industry [25]. However, since these studies did not focus on hand eczema patients, but on a mixture of healthy workers and workers with hand eczema, the results are not directly comparable. Also, most of these studies were cluster-randomised with a high risk of systematic errors (that is risk of overestimation of benefits and underestimation of harms) and random errors (that is play of chance), and two studies focused mostly on use of emollients [18,21]. In addition to the published trials we found one design article on a randomised trial [26]. This trial aims to investigate a guidance programme in self-management chronic hand eczema. The trial is ongoing and results are thus yet unknown.

Overall, randomised clinical trials and a systematic review of the randomised clinical trials indicate a positive effect of prevention programmes for patients with occupational hand eczema. However, we still lack information from large randomised clinical trials with a low risk of bias on the effect of a low-cost group-based education. The PREVEX trial will be the first individually randomised trial to investigate the benefits and harms of group-based education in patients with newly notified occupational hand eczema.

### Objectives

The objectives of the PREVEX trial are to investigate the benefits and harms of a complex intervention consisting of:

A. Group education on general skin-protective behaviour.

B. Job-specific counselling on work-related skin-protective behaviour, which might extend to a work-place visit.

C. Social guidance related to occupational hand eczema.

D. Telephone hotline for work- and patient-related problems, maintained by nurse or medical doctor.

## Methods

### Trial design

The PREVEX trial is a randomised, parallel-group, superiority trial without blinded outcome assessment of the primary outcomes, but several of the secondary outcomes will be blinded (see below) (Figure 1).

**Figure 1 F1:**
[figure not shown]
Trial flowchart.

### Setting and selection of participants

Participants are recruited from the National Board of Industrial Injuries files. These files include information on all notified industrial injuries in Denmark. All individuals from Region Zealand and the Capital Region of Denmark (except the island of Bornholm) with a suspected skin-related industrial injury notified between July 2012 and December 2013 will be invited to participate in the trial. The trial invitation will be sent along with the postal questionnaire, participant information sheet, an informed consent form, and a pre-paid return envelope. All individuals will be encouraged in the invitation to contact the investigators for further information or if they wish for an individual meeting with verbal information. Individuals who return the questionnaire will be eligible for the PREVEX trial, if they comply with the following inclusion and exclusion criteria.

### Inclusion criteria

• Living in Denmark.

• Self-reported hand eczema, i.e., individuals answering ‘yes’ in the questionnaire to the question ‘have you or have you had hand eczema?’

• The questionnaire is sufficiently filled in with respect to ‘severity of hand eczema’ and ‘profession’.

• Written informed consent.

### Exclusion criteria

• Age below 18 years or above 65 years.

• Permanently excluded from the workforce.

• Inability to understand the Danish language sufficiently to benefit from the course.

• Any serious medical condition which, in the opinion of the investigator, may interfere with the evaluation of the results.

• Lack of written informed consent.

### Participant withdrawal and discontinuation of participants

The participants are free to withdraw their informed consent from the trial at any time without effecting future treatment or their case processing in the National Board of Industrial Injuries. If a participant wishes to withdraw his or hers consent, they will be contacted and asked to specify which aspects of the trial they wish to withdraw from: participation in the experimental intervention, participation in follow-up interviews and answering the questionnaires, use of follow-up data collected from national databases, or complete withdrawal from trial, i.e., use of already collected data the analyses.

All participants who enter the trial will be accounted for in the publication of the results. Participants who fail in attending a course on a planned date will be contacted and offered a new course. Participants who cannot be reached during the follow-up period will be contacted and encouraged to resume contact. Participants who do not return the follow-up questionnaire will be contacted and a letter will be sent containing a questionnaire on reasons for drop out.

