#### Follow-up period, from inclusion to 12 months after inclusion

Data on absence from workforce will be collected every eight weeks, by telephone call, e-mail, text message or any other chosen form of media by a blinded investigator, for one year in the intervention group and in the control group. The data will be registered directly in paper record forms by a nurse. Absence will be categorised by participants as: total sick leave; eczema-related sick leave; absence from work for other reasons (child care during illness, etc.); unemployment; and other reasons. Later these data will be entered into SAS by the external assistants.

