#### End of follow-up, 12 months after inclusion

Participants fill in a follow-up questionnaire regarding self-reported level of eczema severity using a photographic guide [29], health-related quality of life (the Dermatology Life Quality Index) [30], level of knowledge concerning prevention of hand eczema, occupational exposure and performance management. The follow-up questionnaire will be distributed by mail to all participants and when returned, entered into SAS by scanning and where that is not possibly, manually, by external assistants. Data on absence from the work force for a period longer than 28 days will be collected from the DREAM register [31]. Further, data regarding potential effect modifiers, i.e., the participants’ use of topical corticosteroids will be collected from The Danish National Database of Reimbursed Prescriptions [32], and visits with a dermatologist will be retrieved from The National Health Insurance Service Registry [33]. Data from both national registers will be collected using the unique Danish Civil Registration Number.

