### Primary outcomes

The PREVEX trial has three co-primary outcomes:

• **Total sick leave**; measured as self-reported total number of days with sick leave during the trial period.

• **Health-related quality of life;** measured as points scored in the Dermatology Life Quality Index (DLQI) at 12 months after inclusion [30].

• **Subjective assessment of hand eczema severity**; measured by use of a photographic guide at 12 months after inclusion [29].

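### The step for participants who do not return the 12-month questionnaire names only a form on drop-out reasons; it should also request the two co-primary outcomes that the questionnaire carries

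*Protocol article*

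**What the plan says.** All references are to the protocol article.

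- *Primary outcomes*: quality of life is "measured as points scored in the Dermatology Life Quality Index (DLQI) at 12 months after inclusion". Severity is "measured by use of a photographic guide at 12 months after inclusion". Each has one post-baseline time point.
- *End of follow-up, 12 months after inclusion*: both come from the same instrument ("Participants fill in a follow-up questionnaire regarding self-reported level of eczema severity using a photographic guide"), and "The follow-up questionnaire will be distributed by mail to all participants and when returned, entered into SAS by scanning". No second source for either outcome is described.
- *Follow-up period, from inclusion to 12 months after inclusion*: every eight weeks participants are contacted "by telephone call, e-mail, text message or any other chosen form of media by a blinded investigator". These contacts collect absence from work, not DLQI or severity.
- *Participant withdrawal and discontinuation of participants*: for non-returners, "Participants who do not return the follow-up questionnaire will be contacted and a letter will be sent containing a questionnaire on reasons for drop out". A separate sentence covers people lost earlier: "Participants who cannot be reached during the follow-up period will be contacted and encouraged to resume contact". The same section lets a participant withdraw specifically from follow-up interviews and questionnaires, as one option among several.
- *Sample size estimation*: the target of 742 is the largest of three calculations.
- *Missing values* and *Sensitivity analyses*: multiple imputation is used if more than 5% are missing on any primary outcome or Little's test is significant. In addition, the observed maximum is imputed in one group and the observed minimum in the other, and then the reverse.

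**The concern.** A participant who does not return one postal form has no post-baseline value for two of the three co-primary outcomes. The plan already includes a contact and a letter to exactly these people, but the instrument it names for the letter carries neither outcome. If the step is carried out as described, the trial learns why the form was not returned but may not obtain the data.

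Two things are at stake. The first is precision, because the sample size has no reserve for loss. The second is bias. Participants know their allocation and only the experimental group attends the course and has the hotline, so return of the form could differ between groups. An observed value, even a slightly late one, is a better safeguard against this than an imputed one.

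**Working it through.** **1. The plan's own figures.** Two-sided α = 0.05/3 gives z = 2.394; 80% power gives z = 0.842. The article does not state sidedness, but two-sided reproduces its numbers.

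- DLQI, difference 1.2, SD 4.8: n per group = 2 × (2.394 + 0.842)² × (4.8/1.2)² ≈ 335.01, rounded up to 336; total 672, as stated.
- Severity, 60% v 48%, pooled variance, no continuity correction: n per group = [2.394 × √(2 × 0.54 × 0.46) + 0.842 × √(0.60 × 0.40 + 0.48 × 0.52)]² / 0.12² ≈ 359.8, rounded up to 360; total 720, as stated.
- Power at 371 per group: DLQI 84.4% (stated 84.3%), severity 81.4% (stated 81.4%).

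These figures are sound.

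**2. Room for loss.** The only slack is the gap between 742 and each outcome's own requirement.

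- DLQI: 742 − 672 = 70, or 70/742 = 9.4%.
- Severity: 742 − 720 = 22, or 22/742 = 3.0%.

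On the sample-size assumptions, severity falls below 80% power before the plan's 5% trigger for multiple imputation is reached.

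**3. Power by loss.** Complete cases, equal loss in both groups, n per group = 371 × (1 − loss). The loss rates are assumptions.

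| Loss | DLQI | Severity |
|---|---|---|
| 5% | 82.2% | 79.0% |
| 10% | 79.8% | 76.5% |
| 20% | 74.3% | 70.6% |
| 30% | 67.5% | 63.8% |

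Recovering half of a 20% loss moves the trial from the 20% row to the 10% row. These are unadjusted two-group calculations, with severity as a yes/no outcome. The planned models adjust for baseline and treat ordinal outcomes by proportional odds, so the table shows direction and rough size, not the trial's actual power.

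**4. Illustration at 18% non-return.** The 82% response in *Expected participant recruitment* comes from a 2002 questionnaire study and is cited there for recruitment. Using it for the 12-month return is an assumption, as are the recovery rates.

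- Missing: 742 × 0.18 ≈ 134; observed ≈ 608.
- One third recovered: 45; still missing 89/742 = 12%.
- One half recovered: 67; still missing 67/742 = 9%; observed ≈ 675.
- Two thirds recovered: 89; still missing 45/742 = 6%.
- Standard error with half recovered, relative to none: √(608/675) = 0.95, a fall of about 5%.

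**5. Effect on the opposite-extreme analysis.** Apply the planned bounds to the 60% v 48% split, with a proportion m missing in each group. In the least favourable case, missing values count as moderate-to-severe in the experimental group and not in the control group:

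difference = [0.48(1 − m) + m] − 0.60(1 − m) = −0.12(1 − m) + m.

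- m = 18%: −0.098 + 0.18 = +0.08. The planned effect reverses.
- m = 9%: −0.109 + 0.09 = −0.02. The direction holds.
- Break-even: m = 0.12/1.12 = 10.7%.

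On these assumptions, halving missingness decides whether the bound keeps the direction of the planned effect.

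**The case against.** The strongest objection is that the sentence describes two acts, a contact and a letter, and gives no purpose for the contact. Neighbouring sentences describe contacts meant to re-engage people, so a reminder to return the form is a natural reading. A condensed article may also leave reminder rounds to the full protocol. This stands: a reader might infer that non-returners are asked only why they dropped out and that the opportunity is wasted, but the text does not establish that. What remains is that the article does name the instrument sent to non-returners, and that instrument carries neither outcome. If the outcomes are also to be requested, the step should say so.

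Other limits also stand:

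- A reader might suppose that many non-returners still answer the eight-weekly contacts. The article gives the schedule of contacts, not retention.
- A reader might suppose that controls get nothing. They have usual care, and the same eight-weekly contacts. Differential return is plausible but not shown.
- Multiple imputation would not be empty-handed. Baseline DLQI and severity, sick-leave reports, and register data on topical corticosteroids and dermatologist visits are all collected and could inform it.
- Even with two thirds recovered, about 6% would be missing in the illustration, still above the 5% trigger.
- Severity needs the photographic guide, which a telephone call or text message may not show. A different mode used only for non-returners could itself introduce a difference in measurement.

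**Conclusion.** The point holds as a cheap improvement to a stated procedure. It is not an error in a figure, and the trial is not invalid without it. Two co-primary outcomes rest on one mailed form, the step for non-returners does not say that they are requested again, and the sample size leaves room for only 9.4% loss on DLQI and 3.0% on severity.

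The likely gain is modest in precision: about 5% in standard error if 18% do not return the form and half of them are recovered. It may be larger for the opposite-extreme analysis. The 18%, the recovery rates, equal loss in both groups and the yes/no form of severity are all assumptions. The illustration also credits the whole recovery to the change, so if the planned contact already includes a reminder that works, the added gain is smaller.

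**What to change.** Amend *Participant withdrawal and discontinuation of participants* as follows:

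1. The contact and letter go to non-returners who have not withdrawn from answering questionnaires. They first request the DLQI and the severity grade, on a short paper form that includes the photographic guide. Drop-out reasons come last.
2. If another medium is used, the guide is supplied to the participant and the blinded contact person collects the answers.
3. Date and mode of completion are recorded, and an acceptance window around 12 months is fixed in advance.
4. A sensitivity analysis leaves out late or other-mode answers.

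The change is mainly to the content of a contact and letter already planned. It adds a short form, a little data entry and one analysis. The downside is that some answers will arrive late or by another mode; items 3 and 4 make that visible but do not remove it.
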